##### Sample Sizing

The size of the AMI group has been based on evaluation of the outcome data at one year from the results of the STEP-IN-AMI trial: a 43% incidence of the primary composite endpoint is expected in the psychotherapy group and 78% in the control group; therefore, 55 pts will be enrolled to achieve statistical power at the 95% confidence level with 80% power. Given the exploratory nature of the study in the other groups, which renders impossible any hypothesis on the effects of psychotherapy, statistical sample sizing has not been performed in these groups. To match the AMI group, 55 women with BC will also be enrolled. However, only 30 patients with TTS will be enrolled for feasibility reasons, due to the lower percentage of patients admitted to the hospital as compared to the other study groups which could unreasonably slow the enrollment phase. Consequently, it will be necessary to enroll 140 HS in the control group.

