## 3. Endpoints and Outcome Measures

(A)Qualitative psychological endpoints:

The baseline and follow-up at one and five years of the psychological features in the four groups of subjects (TTS patients, AMI patients, BC women, and HS) as well as subjects classified according to psychotherapeutic treatment will be assessed by the per-protocol psychometric tests, the two enrollment questionnaires (see below), and the Six Drawing test (6DT).

The following qualitative psychological variables will be evaluated at enrollment and the one-year follow-up:Perception of body and emotions; qualitative analysis will be performed with two questionnaires, administered to all participants: (1) Enrollment body perception questionnaire (Supplementary Material S1); (2) One-year follow-up body perception questionnaire (Supplementary Material S2).Subject’s memory of last week, last month, last year, and past years’ dreams only at enrollment. A qualitative analysis will be performed with two questionnaires, administered to all participants: (1) Enrollment dream questionnaire (Supplementary Material S3); (2) One-year follow-up dream questionnaire (Supplementary Material S4).6DT patterns characteristics

(B)Medical endpoints

Based on the patients’ choice after enrollment, if the size of groups undergoing psychotherapy and those declining is sufficient to allow comparisons, the following medical endpoints will be assessed:-In AMI and TTS pts: the cumulative incidence of new cardiac events (i.e., MI, revascularization, life-threatening ventricular arrhythmias, recurrence of typical angina pectoris, stroke, and death all-cause), plus the occurrence of any clinically significant new medical disorder (active diseases requiring hospitalization or chronic medical therapy, or that cause a transient or permanent physical limitation), at the one and five-year follow-up in patients undergoing psychotherapy plus standard medical therapy and those on standard medical therapy only.-In BC patients: the incidence of breast cancer relapse, metastasis, or the occurrence of any clinically significant new medical disorder (that is an active disease requiring hospitalization or chronic medical therapy, or that cause a transient or permanent physical limitation), at the one and five-year follow-up in patients undergoing psychotherapy plus standard therapy and those on standard therapy only.-In all pts: new hospital admissions.

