## 4. Statistical Analysis

An external committee will evaluate the results in each phase of the research and the characteristics of each group will be analyzed. The qualitative results related to the 6DT, body perception questionnaire, and dream questionnaire at enrollment and the one-year follow-up. It is impossible to foretell the specific features of oneiric symbols and patterns before the study, as the research is a pilot study in the field of psychosomatics. The oneiric manual of the ontopsychological school [45] will be used as an initial reference point for the analysis and classification of dreams.

Unless otherwise specified, all study data will be analyzed on an intention-to-treat basis.

Event rates will be expressed as proportional incidences and as person−time incidence rates. Continuous variables for each of the study groups will be reported as means (with standard deviations or 95% confidence intervals) or as medians (lower quartile-upper quartile), as appropriate; categorical variables will be reported as absolute numbers and percentages. Continuous unpaired variables will be compared using the independent-sample Student’s t or Mann-Whitney U tests, and continuous paired variables will be compared using paired Student’s t or Wilcoxon tests, as appropriate. Categorical variables will be compared by Pearson’s chi-squared analysis or Fisher’s exact test, as indicated. The outcome incidence within each study group over long-term follow-up will be compared with Friedman’s test. Survival analysis will be performed using Cox proportional hazards ratios. Multivariable binary logistic regression analysis will be performed to appraise the independent predictive role of baseline characteristics on outcomes. Spearman’s rank correlation test will be performed to assess the correlation between variables. A *p* value < 0.05 will be considered statistically significant, with all inferential tests 2-tailed. Statistical analysis will be performed using the statistical software program SPSS, version 11.5 (SPSS Inc., Chicago, IL, USA).

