## 5. Discussion

The PSYCHONIC study is an observational research protocol, primarily designed to obtain at enrollment a qualitative analysis of distinctive psychological characteristics of patients suffering from different NCDs: ischemic heart disease, Takotsubo syndrome, and breast cancer, and comparing them to age and sex-matched control subjects without major diseases. Some psychological areas are explored systematically for the first time: “body perception”, dream patterns, and the 6DT. We are exploring new hypotheses which may highlight possible specificities or similarities in different clinical presentations.

From a psychoanalytic perspective, and especially for ontopsychology, dream material and analysis are a fundamental part of the theory and for the psychotherapeutic approach. In this observational trial, we hypothesize that comparing psychosomatic characteristics in different clinical settings may shed light on pathophysiologic and clinical issues and provide novel working hypotheses. This study, addressing cardiologic and non-cardiologic syndromes together, may appear non-coherent from a classic perspective. However, this study design has the potential to address possible underlying common pathogenic processes shared among different diseases beyond the reductionist splitting of the human being according to an organ or clinical presentation.

Despite observational studies’ inherent, well-known limitations, they complement randomized controlled trials (RCTs) in several aspects. RCTs are poor in assessing the generalizability of an intervention whereas observational trials can address this issue with an intervention that has been proven internally effective in RCTs. In this case, the STEP-IN-AMI trial provided good randomized evidence of the efficacy of ontopsychological psychotherapy after AMI in selected patients, but it is still unknown to what extent this can be extrapolated to the real world.

The results of the PSYHCONIC study have been designed to shed light on some possible underlying mechanisms and therefore generate new working hypotheses to better target interventions. Therefore, it may help in assessing the efficacy of ontopsychological psychotherapy after AMI in the real world and in preliminarily testing the hypothesis of its efficacy in other NCDs.

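### Psychological scores are compared across AMI, TTS, breast cancer and healthy groups without age or sex adjustment, although breast cancer is all women, so a sex difference can pass for a disease profile

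*Protocol article*

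**What the plan says.** Section 5 (Discussion) states the main purpose as "a qualitative analysis of distinctive psychological characteristics of patients suffering from different NCDs". The same sentence adds a comparison with age- and sex-matched controls, and the paragraph goes on to look for specificities or similarities between clinical presentations. Section 3, part A, assesses "psychological features in the four groups of subjects (TTS patients, AMI patients, BC women, and HS" and classifies subjects by psychotherapy as well. Section 3.2.1 evaluates differences and peculiar characteristics at enrollment.

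On comparability, Section 2.2.1 matches only the healthy subjects (HS) on age and sex. All patients must be 30 to 75 years old. No sex restriction is given for AMI or Takotsubo syndrome (TTS). For breast cancer, the Sample Sizing paragraph says "To match the AMI group, 55 women with BC will also be enrolled", which is a match in number. TTS has 30 patients and HS 140.

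On analysis, Section 4 says "Continuous unpaired variables will be compared using the independent-sample" Student's t or Mann-Whitney U test. It says "Categorical variables will be compared by Pearson" chi-squared or Fisher's exact test, and "The outcome incidence within each study group over long-term follow-up will be compared with Friedman" (Friedman's test). Multivariable logistic regression is named to find which baseline characteristics predict outcomes. The threshold is a p "value < 0.05 will be considered statistically significant, with all inferential tests 2-tailed".

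**The concern.** To call a trait specific to a disease, one has to compare diseases with each other as well as with healthy people. The design does not balance sex or age between the diseases. For breast cancer the sex imbalance is built in, unless the AMI or TTS group happens to be all women.

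The analysis named for continuous scores cannot correct this, because a t or Mann-Whitney test carries no covariate. The scores concerned are those Section 3.1 gives to all four groups: self-evaluation, social support, BDI, STAI and STAXI-2. The categorical tests are equally unadjusted, so coded dream, body-perception and drawing categories are exposed too. Friedman's test works within a group.

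The article wants its working hypotheses to help target interventions. A trait that follows sex or age but is reported as belonging to a disease would give a wrong hypothesis.

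**Working it through.** **The article's own figures.** The AMI sample size does not bear on this point, but it reproduces. With the unpooled formula, n per arm = [0.43×0.57 + 0.78×0.22] × (1.960 + 0.842)² / (0.78 − 0.43)² = 0.4167 × 7.849 / 0.1225 = 26.7. That is 27 per arm and 54 in total, against 55 stated. HS: 55 + 55 + 30 = 140, as stated.

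**Inputs from the article.** AMI 55, BC 55 (all women), TTS 30, HS 140; two-sided 0.05; no covariate in the between-group tests of continuous scores.

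**Assumptions, not in the article.** Share of women in AMI, f = 20-50%. Sex difference in a score, s = 0.3-0.5 SD. No disease effect. For the contrasts with HS only, TTS is about 90% women and the HS sex mix follows that of all patients.

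**AMI v BC.** The spurious difference is d = s × (1 − f). The t-test noncentrality is d / √(2/55), with √(2/55) = 0.191 and 108 degrees of freedom.

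| f | s | d (SD) | noncentrality | rejected (noncentral t) | rejected (simulated) |
|---|---|---|---|---|---|
| 20% | 0.3 | 0.24 | 1.26 | 24% | 24% |
| 20% | 0.5 | 0.40 | 2.10 | 55% | 53% |
| 30% | 0.3 | 0.21 | 1.10 | 19% | 19% |
| 30% | 0.5 | 0.35 | 1.84 | 44% | 44% |
| 50% | 0.3 | 0.15 | 0.79 | 12% | 12% |
| 50% | 0.5 | 0.25 | 1.31 | about 25% | 25% |

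The nominal rate is 5%. The simulation is slightly lower at the top because a mixed-sex AMI group also has a larger variance.

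**Disease v pooled HS.** At f = 20%, HS would hold about 55 + 11 + 27 = 93 women of 140 (66%), against 100% in BC and 20% in AMI. At f = 50% the figure is about 110 of 140 (79%). Over the same range of f and s, simulated rejection is 6-17% for BC v HS and 8-29% for AMI v HS. Matching HS to the patients as a whole therefore does not balance sex within a single disease's contrast.

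**With sex in the model.** False rejection returns to about 5%. The price is precision. For a four-group model with a common sex effect, Var(BC − AMI) in SD² units is 2/55 + (1 − f)² / W, where W is the within-group sum of squares of the sex indicator. At f = 20%, W = 55×0.2×0.8 + 30×0.9×0.1 + 93×47/140 = 8.8 + 2.7 + 31.2 = 42.7. The variance is 0.0364 + 0.64/42.7 = 0.0514, so the standard error is 0.227 against 0.191 unadjusted, about 19% larger.

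**Women only.** At f = 20-30%, 11-17 AMI women face 55 BC patients. Power for a 0.5 SD difference is then 32-43%, against 74% for 55 v 55.

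**The case against.** The strongest reply is that the article does name a control for age and sex. The sentence in Section 5 on distinctive characteristics goes on to the matched healthy subjects, and 140 HS correspond to 140 patients. Section 3.2.2 lists four research areas, none of which is disease v disease, and two-sample tests suit the psychotherapy v no-psychotherapy comparisons there. This stands in part. If each disease were compared with its own matched HS, age and sex would be controlled in that contrast. But the article treats HS as one group and mentions no matched subsets, and HS matching cannot help when diseases are compared with each other, as the search for specificities requires.

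A second reply is that covariates are often left to a fuller document. That would answer silence. Here the article names the tests, and those named do not take account of the imbalance.

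A third reply is that the sex mix and the sex effect are assumed. That is correct, and it limits the size of the problem, not its existence: BC is women only by design.

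Two stronger readings are tempting and not supported:

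- A reader might infer that the article names only two-sample tests. That is true for unpaired continuous variables only. Chi-squared and Fisher's exact test handle four groups and would suit the coded qualitative material.
- A reader might infer that six pairwise comparisons at 0.05 make a false claim of disease specificity likely. The article plans no set of six tests, and one significant pair among six is not such a claim. In work described as a pilot exploring new hypotheses, a multiplicity correction, an overall test as gatekeeper, or a rule that a feature must differ from every other group is a matter of preference.

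**Conclusion.** The point holds as a confounding problem. The article compares psychological features across groups that differ in sex by design and may differ in age, and the between-group tests it names adjust for neither. On the assumed 20-50% women in AMI and a 0.3-0.5 SD sex difference, an AMI v BC t-test is falsely significant in about 12-55% of studies, and BC v pooled HS in 6-17%. The second range also rests on the assumed TTS and HS sex mix. Age imbalance is not quantified: the common 30-75 limit narrows it without removing it. The exploratory aim makes multiplicity a minor matter but does not excuse the confounding. This is an inexpensive improvement to the analysis and does not invalidate the study.

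**What to change.** In Section 4, for each baseline feature given to all four groups, replace the unadjusted between-group tests with one model (linear for scores, logistic for coded categories) containing four-level group, age and sex. Report adjusted contrasts with 95% confidence intervals.

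For disease v healthy contrasts, use that model or each disease's own matched HS, and say which. Give women-only BC contrasts as a sensitivity analysis. Label pairwise results exploratory.

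The change is wording: demographics are collected at enrollment (Section 3.2.1), and 75 of 280 subjects had been enrolled at the time of writing. The cost is lower precision for AMI v BC, because few AMI patients may be women. The adjusted contrast also leans on an assumed common sex effect, which the women-only analysis checks, though with low power.

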#### 3.2.3. Follow-Up

Follow-up is planned at one and five years with a comprehensive medical visit and yearly routine blood tests.

For AMI pts, echocardiography, an exercise stress test, or stress myocardial perfusion scintigraphy, will be performed when medically indicated.

For TTS pts echocardiography is timetabled at one month and six months after the acute phase, and yearly through the five-year follow-up when indicated.

For BC pts, history, physical examination, and mammography will be obtained at follow-up. Physical examination is planned every 3 to 6 months for the initial 3 years, every 6 to 12 months for years 4 and 5, and annually thereafter. For women who have undergone breast-conserving surgery, a post-treatment mammogram is scheduled 1 year after the initial mammogram and at least 6 months after completion of radiation therapy. Thereafter, unless otherwise indicated, a yearly mammogram will be scheduled. The use of complete blood counts, chemistry panels, bone scans, chest radiographs, liver and pelvic ultrasound, computed tomography scans, fluorodeoxyglucose–positron emission tomography scans, magnetic resonance imaging, and/or tumor markers (carcinoembryonic antigen, CA 15-3, and CA 27.29) are not recommended for routine follow-up in an otherwise asymptomatic patient with no specific findings on clinical examination [56].

At the one-year follow-up all patients and HS will be administered: (a) the same psychometric tests administered at enrollment; (b) two qualitative questionnaires, the 1-year follow-up body perception questionnaire (Supplementary Material S2), and the 1-year follow-up dream questionnaire (Supplementary Material S4); (c) the 6DT.

At the five-year follow-up, all psychometric tests will be administered to all of the groups.

Data will be recorded on paper case-report forms and transferred into an electronic database, with the principal investigator cross-checking consistency of data for all patients.

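### Friedman's test on outcome incidence over follow-up gives a p value that counts new events and does not test for a change in risk

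*Protocol article*

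**What the plan says.** Section 4 of the protocol article (Statistical Analysis) fixes one method for the course of outcomes over time: "The outcome incidence within each study group over long-term follow-up will be compared with Friedman’s test". Significance is set in the same section: "A *p* value < 0.05 will be considered statistically significant, with all inferential tests 2-tailed".

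Section 3 (Endpoints and Outcome Measures) defines the outcome. For infarction and Takotsubo patients it is "the cumulative incidence of new cardiac events (i.e., MI, revascularization, life-threatening ventricular arrhythmias, recurrence of typical angina pectoris, stroke, and death all-cause", plus any clinically significant new medical disorder, assessed at one and five years. For breast cancer patients it is "the incidence of breast cancer relapse, metastasis, or the occurrence of any clinically significant new medical disorder", at the same times, without the word cumulative.

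Section 3.2.3 gives the visits: "Follow-up is planned at one and five years with a comprehensive medical visit and yearly routine blood tests". Section 4 also plans "Event rates will be expressed as proportional incidences and as person−time incidence rates" and "Survival analysis will be performed using Cox proportional hazards ratios". The Friedman sentence does not say which scale of incidence it uses, or whether baseline counts as a time point.

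Section 3.2.2 splits the sample into seven study groups: each disease with and without psychotherapy, plus the healthy subjects. The test is therefore run inside the divided groups.

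**The concern.** Friedman's test asks whether repeated measurements on the same subjects differ in level between occasions. It informs only if the level could move either way. A patient who has had an event by year 1 still counts as having had it by year 5, so every within-patient change in a cumulative outcome has the same sign. A small p value then says that some first events came after year 1, which nobody doubted. It does not say that risk rose, fell or stayed the same.

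At stake is the reading of the results. The plan would yield a separate p value for the psychotherapy group and the standard-therapy group of each disease. If one is below 0.05 and the other is not, this can look like a difference in prognosis, although it may reflect only group size or event count.

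**Working it through.** **Inputs from the protocol article.** Time points 1 and 5 years; two-sided alpha 0.05; 55 infarction, 55 breast cancer and 30 Takotsubo patients before division by treatment choice; Takotsubo choices so far 15 for psychotherapy and 4 against (Enrollment Status). The only event rates given are one-year rates for infarction: "a 43% incidence of the primary composite endpoint is expected in the psychotherapy group and 78% in the control group".

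**Assumptions.** Constant hazard; one-year risks of 5% and 10%; group sizes of 27 (about half of 55), 15 (half of 30) and 6 (30 × 4/19 = 6.3, if the present Takotsubo split held). The protocol says that the split cannot be foretold.

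**The plan's own figure.** None is attached to this test. The one computed figure, 55 infarction patients, is roughly reproduced by (1.96 + 0.842)² × (0.43 × 0.57 + 0.78 × 0.22) / 0.35² = 26.7 per arm, or 54 in total. The point does not depend on it.

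**Step 1: cumulative outcome, year 1 against year 5.** For 0/1 data at two times, Friedman's statistic with tie correction is (b − c)²/(b + c). Here b is the number of patients who go from no event to event, and c the number who go the other way. With a cumulative outcome c = 0, so the statistic is b. The critical value is 3.84 on 1 degree of freedom:

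- b = 3: p = 0.083
- b = 4: p = 0.0455

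The number of patients in the group does not enter.

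**Step 2: with an event-free baseline as a third time point.** Three patients with an event by year 1 and none later give p = 0.0498. Every split of four events between the two periods gives p < 0.05 (largest 0.0498, for two and two).

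**Step 3: how often four new first events occur under a constant hazard.** With one-year risk r, a patient's chance of a first event between years 1 and 5 is (1 − r) − (1 − r)⁵.

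- r = 0.10: 0.9 − 0.5905 = 0.3095
- r = 0.05: 0.95 − 0.7738 = 0.1762
- r = 0.43: 0.57 − 0.0602 = 0.5098
- r = 0.78: 0.22 − 0.0005 = 0.2195

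The binomial chance of at least four such patients is:

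| One-year risk | n = 27 | n = 15 | n = 6 |
|---|---|---|---|
| 10% (assumed) | 98% | 73% | 8% |
| 5% (assumed) | 73% | 26% | 1% |
| 43% (protocol, infarction) | >99.9% | 99% | 36% |
| 78% (protocol, infarction) | 87% | 43% | 2% |

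The hazard never changes in any of these cells.

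**Step 4: incidence per interval.** Suppose instead that each patient is scored for any event in years 0–1 and any event in years 1–5, with recurrence allowed and a constant hazard. Then b has probability [1 − (1 − r)⁴](1 − r) and c has probability r(1 − r)⁴. For r = 0.10 these are 0.3439 × 0.9 = 0.3095 and 0.1 × 0.6561 = 0.0656. The second interval is four times as long and the test has no exposure term, so b exceeds c although the rate is the same. Exact enumeration of (b − c)²/(b + c) > 3.84 gives rejection in about 55% of groups of 27 and 34% of groups of 15. At r = 0.43 and n = 27 it is about 96%. The nominal level is 5%.

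**Step 5: same prognosis, different group size.** At the present split, 30 Takotsubo patients would divide into about 24 and 6. With the same assumed hazard of 0.10 per year in both groups, the year 1 against year 5 test reaches p < 0.05 with probability 96% in the larger group and 7% in the smaller.

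**The case against.** The best defence has four parts.

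- **The scale is not stated.** The sentence speaks only of outcome incidence, and cumulative is attached only to the infarction and Takotsubo composite. An article may leave such detail to a fuller document. This stands as a limit on the first argument: that the level can only rise is explicit for two diseases, not for breast cancer. It does not rescue the test, because step 4 shows that the per-interval reading fails for another reason.
- **The test is legitimate in itself.** On 0/1 repeated data it equals Cochran's Q. That is correct. The fault lies in using it for a monotone outcome, or for intervals of unequal length.
- **Suitable methods are already planned.** The Cox model and person-time rates handle censoring and unequal time, and the psychotherapy comparison does not rest on Friedman's test. This stands, and it lowers the weight of the point.
- **The size of the problem varies.** A reader might infer that the test will be significant in almost any group, perhaps from the undivided totals of 30 and 55. The protocol does not support that: the test is run within each study group, and Section 3.2.2 divides each disease by treatment choice. In small or low-risk groups four new first events will often not occur.

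A reader might also take the need for complete rows as a separate fault. Handling of missing visits may be set out elsewhere and is not counted here.

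**Conclusion.** The concern holds in limited form. For the cumulative infarction and Takotsubo endpoint the null hypothesis is false by construction after one later first event, and the p value carries only the event count. This part is algebra on the protocol's definitions and needs no assumed rate. If incidence per interval was meant, for breast cancer or in general, the test is still unsuitable because it takes no account of time at risk.

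The rejection probabilities rest on an assumed constant hazard, assumed group sizes and, for the 5% and 10% rows, assumed risks. They run from about 1% to near certainty, so no general statement about how often the test will be significant is justified. Severity is modest: this is one secondary within-group line in a largely exploratory observational study, but as written it would produce p values that mislead.

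**What to change.** - Delete the Friedman sentence for event outcomes in Section 4.
- Report cumulative incidence with 95% confidence intervals at one and five years in each group.
- If periods are to be compared, use the person-time rates already planned, years 0–1 against years 1–5, for example as a rate ratio with its confidence interval. A Poisson model with a log person-time offset and robust standard errors is one way among several.
- State that any comparison of psychotherapy with standard therapy rests on the planned Cox model and not on separate within-group p values.

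The cost is one deleted sentence and two or three new ones. No new data, visits or patients are needed.

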#### 3.2.2. Treatment Choice, Implementation, and Group Allocation

In the second phase, all pts with TTS, AMI, and BC will be asked to freely choose between ontopsychological STP along with standard medical therapy and, whenever indicated, rehabilitation therapy or medical therapy plus rehabilitation alone.

Therefore, this phase results in seven study groups: three groups of pts (AMI, TTS, and BC) undergoing psychotherapy, three groups of pts (AMI, TTS, and BC) on standard medical therapy, and one group of HS.

There will be four independent areas of research: (1) AMI pts following psychotherapy (AMI-PSY) will be compared with AMI pts, without psychotherapy (AMI-C); (2) TTS pts who will follow psychotherapy (TTS-PSY) will be compared with TTS pts without psychotherapy (TTS-C); (3) BC pts with psychotherapy (BC-PSY), will be compared with BC pts without psychotherapy (BC-C); (4) HS subjects, after the initial comparative evaluation with the other enrolled groups, will have an independent follow-up, where psychological data collected at enrollment will be compared with psychological data collected at one year and with clinical follow-up at five years.

Since the research is observational, it is not possible to foretell how many patients will choose psychotherapy plus medical therapy or standard medical care alone.

If balanced patient groups can be formed, statistical analysis evaluating differences between groups will be performed. Thus, it may be possible to evaluate how psychotherapy may impact the real world because patients will have a choice between psychotherapy plus medical care or medical care alone. It will also be possible to evaluate if psychotherapy might result in an improvement in psychological patterns compared to medical therapy alone, and how this can translate in an improvement in medical prognosis. Moreover, the patients’ choice might provide useful information to improve a more individualized therapy and hospital organization.

AMI-PSY and TTS-PSY patients will be referred to the outpatient clinic of Cardiac Psychology at San Filippo Neri Hospital in Rome; BC-PSY will be referred to the outpatient clinic of Psycho Oncology in the same hospital. Psychotherapy will be provided in individual sessions (maximum of ten) and five group meetings, as in the STEP IN AMI trial. Psychotherapy will be conducted by two expert psychotherapists trained in ontopsychology and psychosomatics.

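### Baseline predictors of outcomes up to five years are assigned to logistic regression, which ignores follow-up time, although the plan already contains a Cox model

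*Protocol article*

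**What the plan says.** Section 4 (Statistical Analysis) of the protocol article sets out several methods for outcomes:

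- Reporting of rates: "Event rates will be expressed as proportional incidences and as person−time incidence rates".
- Time to event: "Survival analysis will be performed using Cox proportional hazards ratios".
- Change within a group over time: "The outcome incidence within each study group over long-term follow-up will be compared with Friedman’s test".
- Baseline predictors: "Multivariable binary logistic regression analysis will be performed to appraise the independent predictive role of baseline characteristics on outcomes".

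The last sentence names no time horizon. It is the only place where a multivariable model is tied to the question of which baseline characteristics independently predict outcomes.

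That question is central to the study. The Abstract lists it first among the endpoints, and section 2.1 (Aims) includes the correlation of baseline psychological data with study outcomes. Section 3 (Endpoints and Outcome Measures) defines the medical endpoint in the infarction and Takotsubo patients as "the cumulative incidence of new cardiac events" together with new medical disorders, at one and five years. Breast cancer has a parallel endpoint at the same two times.

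On contact with patients, section 3.2.3 says: "Follow-up is planned at one and five years with a comprehensive medical visit and yearly routine blood tests". Therapy is the patient's own choice, and section 3.2.2 warns that "it is not possible to foretell how many patients will choose psychotherapy plus medical therapy or standard medical care alone". For those who choose it: "Psychotherapy will be provided in individual sessions (maximum of ten) and five group meetings".

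**The concern.** A binary logistic model needs a yes or no for every patient at a fixed time. A patient who had an event before leaving still supplies a yes. A patient who leaves event-free in, say, year two supplies neither, and the analyst has two options. Excluding such patients keeps the leavers with events and discards those without, so risk is overstated. Coding them as non-events credits them with event-free years that nobody observed, so risk is understated.

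If leaving is unrelated to any covariate, this mainly shifts the overall level of risk. If leaving depends on a baseline trait, the shift differs between levels of the trait, and the trait acquires a spurious odds ratio. Its direction depends on how leavers are handled.

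The design gives some reason to expect such dependence. Patients choose their therapy, the study itself looks for psychological predictors of that choice, and those who choose psychotherapy have up to 10 + 5 = 15 additional contacts with the hospital. A trait that leads to psychotherapy could therefore also lead to better retention. The documents do not show that this happens; it is a plausible route.

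**Working it through.** **The plan's own figures.** The article gives neither a loss rate nor a five-year risk. The only related figure is the infarction sample size: 43% versus 78% at one year, two-sided 5%, 80% power, 55 patients. The unpooled two-proportion formula gives

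n per group = (1.960 + 0.842)² × (0.43 × 0.57 + 0.78 × 0.22) / 0.35² = 26.7, so 27 per group and 54 in total.

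This is close to the stated 55. It uses one-year rates and no loss, so it neither supports nor weakens the present point.

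**Assumptions for the illustration** (none is in the documents):

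- two groups with the same true five-year risk R, 50% or 70%;
- loss over five years L of 10% in one group and 30% in the other;
- constant hazards, with leaving independent of the event.

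**Formulas.** Event hazard h = −ln(1 − R)/5 and loss hazard c = −ln(1 − L)/5.

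- Events observed before leaving: E = h/(h + c) × [1 − exp(−5(h + c))].
- Followed to five years without an event: F = exp(−5(h + c)) = (1 − R)(1 − L).
- Proportion with leavers coded event-free: E.
- Proportion with event-free leavers dropped: E/(E + F).
- Person-time: P = [1 − exp(−5(h + c))]/(h + c), so the rate E/P equals h whatever the loss.

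**R = 50%**, h = 0.1386 per year:

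| | L = 10% | L = 30% |
|---|---|---|
| c per year | 0.0211 | 0.0713 |
| E (coded event-free) | 47.7% | 42.9% |
| F | 45.0% | 35.0% |
| E/(E + F) (dropped) | 51.5% | 55.1% |
| Person-time rate per year | 0.1386 | 0.1386 |

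With leavers dropped, the gap is −3.6 points (odds ratio 0.87). With leavers coded event-free it is +4.8 points (odds ratio 1.22). The true odds ratio is 1.00 and the person-time rate ratio is 1.00.

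**R = 70%**: dropped, 71.3% versus 74.4% (odds ratio 0.86); coded event-free, 67.1% versus 60.9% (odds ratio 1.31).

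**Range.** With true risks of 43%, 60% and 78% and loss pairs of 10/30%, 5/30% and 10/40%, the spurious odds ratio is 0.77 to 0.87 with exclusion and 1.19 to 1.62 with coding as non-events. The person-time rate ratio is 1.00 throughout.

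**What this measures.** These are crude gaps between two groups. They carry over to a two-level baseline trait only if loss differs as strongly between its levels. A weaker link gives a smaller distortion, and no adjusted odds ratio from a multivariable model has been calculated.

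**The case against.** The strongest reply is that the plan already uses the follow-up of early leavers. A reader might infer that five-year outcomes are reported only as simple proportions and that all the rates are therefore biased. Section 4 does not support that: the sentence on event rates also promises person-time incidence rates, and Cox regression is planned. Under non-informative loss, neither has the bias shown above. It affects only the accompanying proportions, tests built on them, and the logistic model.

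A reader might also infer that logistic regression loses everyone who leaves early. It does not, because leavers with a prior event remain usable.

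A third inference would be that retention does differ by therapy choice. The article reports no loss at all, and patients who decline psychotherapy have other contacts. Section 3.2.3 schedules yearly blood tests, regular breast cancer examinations and Takotsubo echocardiography, and section 2.3 refers infarction patients to cardiac rehabilitation. Differential loss is possible but not shown.

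Two further objections carry weight. The illustrated gaps are small beside sampling error: with 27 per group and 50% risk, the standard error of a difference is √(2 × 0.25/27) = 0.136, or about 14 points. And rules for missing outcomes may sit in a full plan that is not shown, so their absence from the article is no fault.

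What remains is the stated choice of model. The logistic sentence names no horizon and also covers one-year outcomes, for which it may serve well. Nothing in the article bars covariates from the Cox model. Even so, the article names logistic regression, and no other multivariable model, for independent prediction of outcomes that run to five years.

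**Conclusion.** The point holds as a matter of model choice. The plan assigns independent prediction of outcomes, including medical events over five years, to a method that ignores follow-up time, while a method that uses it is already in the plan. It does not hold as a claim that the event rates as a whole are biased.

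The size is conditional. With equal true risk of 50% or 70% and loss of 10% versus 30%, a spurious gap of about 3 to 6 points appears, with its sign set by how event-free leavers are handled. With equal loss in the two groups the spurious gap disappears, though each proportion is still shifted. With informative loss, the Cox model and person-time rates would be biased too. The change is worth making because it costs little, not because a large error has been shown.

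**What to change.** 1. Fit baseline predictors of the five-year medical outcomes in the Cox model already planned, with censoring at last contact.
2. Keep logistic regression for the choice of psychotherapy, where every patient's status is known, and for one-year outcomes if status is near-complete.
3. Accompany the five-year proportions with Kaplan-Meier or cumulative incidence estimates.
4. Record endpoint events with their dates, and vital status, at the yearly contacts already scheduled. A patient who misses the five-year visit is then censored at the last yearly contact.

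The cost is a revised sentence in the analysis section and a short event checklist at existing contacts. When the article was written, 75 of 280 subjects had been enrolled, so dated recording could still start from entry for the remaining 205. The downside is that event dates are required, and that Cox regression assumes proportional hazards and loss unrelated to risk given the covariates. Both assumptions should be examined and reported.
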